follow-up (LTFU) to the national PMTCT/ART program (defined by the MOH as all those who have not returned to the clinic for more than 2 months after the date when they were expected to run out of antiretrovirals and are not documented as having transferred out, stopped ART, or died); 2) mortality is 30% among HIV-infected mothers who are LTFU; and 3) a coefficient of variation of 0.15 should be adequate to obtain relatively conservative projections of precision in each joint stratum. Applying these considerations to our MIP target population, we will select between 66% and 100% of high-volume sites and about 30 MIPs at each site from across the 20 joint strata to enrol our nested cohort (**Table 3**).

**Table 3:** Illustrative sampling approach for individual mother-infant pairs at facility catchment area level.

| Joint stratum number | Total high-volume catchment areas in strata | Expected catchment areas sampled (66 - 100%) | Expected Range of number of PMTCT mothers available for sampling per joint stratum | Approximate Total Mothers sampled | Approximate Mothers with complete routine care data (.73 SOC, .80 CFLs) | Approximate Mothers Needing Tracing (0.27 SOC, 0.20 CFLs) |
|----------------------|---------------------------------------------|----------------------------------------------|------------------------------------------------------------------------------------|-----------------------------------|-------------------------------------------------------------------------|-----------------------------------------------------------|
| 1*                   | 0                                           | 0                                            | 0                                                                                  | 0                                 | 0                                                                       | 0                                                         |
| 2                    | 0                                           | 0                                            | 0                                                                                  | 0                                 | 0                                                                       | 0                                                         |

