#### **Primary Outcome:**

- 12-month post-ART initiation retention in care for HIV-positive mothers

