#### **Secondary Outcomes:**

- Proportion of pregnant women newly registered in ANC who received HIV testing services
- Proportion of HIV-infected PMTCT clients initiated on anti-retroviral therapy
- 6-month post-ART initiation retention in care for HIV-positive mothers
- Proportion of HIV-positive mothers achieving HIV virological suppression from 6 months post-ART initiation (at MOH-recommended times of 6 and 24 months post-ART and, through the study, at time points between 12 and 24 months post-ART initiation)
- 12-month infant HIV-free survival
- Exposed infant “early” HIV infection status (i.e. HIV-1/2 DNA PCR result) from age 6 weeks
- 24-month child HIV-free survival
- 12- and 24-month infant HIV sero-status
- Median time from PMTCT enrolment to maternal ART initiation
- Median age of ART initiation for HIV-infected infants and young children
- Proportion of HIV-infected infants and young children achieving HIV virological suppression (from 6 months post-ART initiation per MOH guidelines)

- Proportion of HIV-infected mothers and infants who “returned to care” within 30 and 60 days of meeting the national ART program definition of loss to follow-up/ “defaulting” (i.e. not known to have transferred out, stopped or died AND have not returned to the clinic for 2 months after the woman is expected to have run out of ARVs).
- Proportion of HEIs who “returned to care” within 30 and 60 days of meeting the national HIV Care Clinic (HCC) programme definition of loss to follow-up/ “defaulting” (i.e. not known to have transferred out, stopped or died AND have not returned to the clinic for 2 months after the “next appointment date” given at the last HCC visit).

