## **7.2.2 Analysis Plan for Objective 2 & 2a**

### **7.2.2.1 Cohort Data**

We will calculate maternal retention in care as the proportion of mothers alive and in care at 6, 12, and 24 months post-ART initiation among all eligible women at the start of the cohort. We will also calculate median days from PMTCT enrolment to ART start to examine the effects of CFL models on time to ART initiation. We will look for differences in the delay of ART initiation across the CFL models and SOC using the Aalen-Johansen estimator to account for the competing event of death. We will report crude HEI mortality at 12 and 24 months as part of our survival analysis. We will define infant 12-month HIV free survival as the proportion of HEIs alive with a negative 12-month HIV-rapid test among all infants enrolled in the HEI birth cohort. Similarly, we will define infant 24-month HIV free survival as the proportion of HEIs alive with a negative 24-month HIV-rapid test among all infants enrolled in the HEI birth cohort. We will use Kaplan Meier techniques to compare infant HIV-free survival at 12 and 24 months across the 3 CFL models and SOC accounting for informative censoring and differences in baseline patient characteristics between the models using inverse probability weights. We will censor all survival outcomes on the last date of field activities in a given district (most likely between February 1, 2018 and April 30, 2019, depending on the district), the date of transfer, or the date of the last clinical encounter, as appropriate.

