We will explore associations between CFL model and individual-level maternal care retention and infant HIV-free survival at 12 and 24 months using multivariate log binomial regression modelling. We will estimate the effect of receiving any CFL service on the risk of 12-month maternal LTFU and viral suppression, controlling for other measured individual- and catchment area-level covariates, including age, pregnancy number, district, facility type, and number of women registered in the PMTCT cohort, among others; we will conduct a sub-group analysis for women who initiated ART while breastfeeding. We will repeat this analysis to examine effects of CFL model components—including client-to-provider ratio, frequency of provider-client interaction, pro-active versus reactive visit adherence approach, presence of CFL provider remuneration, CFL provider training frequency and duration, availability of one-on-one psychosocial support, and other variables—on maternal 12-month LTFU, maternal viral

suppression, and infant 12- and 24-month HIV-free survival. For maternal viral suppression, we will use survival analysis methods to control for variability in the timing of outcome ascertainment and to enable comparison of viral suppression between groups accounting for interval censoring. For the 24-month HIV-free survival outcome, we will control for infants who do not reach 24 months of age by the time of outcome ascertainment by excluding them from the analysis (so that the outcomes for all infants are represented by those who made it to 24 months in the study). As a check on the robustness of this approach, we will conduct a sensitivity analysis and use inverse probability weighting of those with outcomes at 24 months (compared to the total study sample) to account for any potential differences between infants who have and do not have a 24-month outcome at the time of field outcome ascertainment. Risk differences, unadjusted risk ratios, and adjusted risk ratios with accompanying 95% confidence intervals will be estimated for each model. Of note, these estimates will include the MIPs lost to routine care who are traced through the study, therefore allowing for more robust estimates of true outcomes in the study cohort.

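### The pooled any-CFL and component regressions name 12-month loss to follow-up as the maternal outcome, which is not the complement of the primary outcome, retention

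*Protocol*

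**What the plan says.** Protocol 7.1 names one primary outcome: "12-month post-ART initiation retention in care for HIV-positive mothers". Section 7.2.2.1 calculates it as "the proportion of mothers alive and in care at 6, 12, and 24 months post-ART initiation among all eligible women", counted from the start of the cohort. Section 6.4 sizes the nested cohort on this outcome: 73% retained under the standard of care (SOC), an 8-point difference between mothers who do and do not receive CFL services, two-sided alpha 0.05, 80% power, 894 CFL and 298 SOC mothers.

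Section 7.2.2.1 then describes the regressions.

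- By model: "We will explore associations between CFL model and individual-level maternal care retention and infant HIV-free survival at 12 and 24 months", using log binomial regression.
- Pooled: "We will estimate the effect of receiving any CFL service on the risk of 12-month maternal LTFU and viral suppression", adjusted for individual and catchment-area covariates.
- Components (Objective 2a): the pooled analysis is repeated for CFL components, again with 12-month maternal LTFU.

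LTFU is defined twice. Section 6.4.1 limits it to women more than 2 months past the date their drugs should have run out who "are not documented as having transferred out, stopped ART, or died". Section 7.1, in the return-to-care outcome, has "not known to have transferred out, stopped or died AND have not returned to the clinic for 2 months".

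For planning, 6.4.1 assumes 73% alive and in care, 4% transferred out, stopped or dead, and 23% LTFU. It adds that "mortality is 30% among HIV-infected mothers who are LTFU".

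**The concern.** The contrast that carries the sample size is any CFL versus SOC on retention. When the analysis section specifies that contrast with covariate adjustment, it names a different maternal outcome. The component hypothesis in section 4.0 also concerns retention, yet the component models use LTFU.

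The two outcomes treat death and stopping ART differently. Under retention, a mother who has died or stopped is a failure. Under LTFU as defined, with all eligible women in the denominator, she is not an event. The study's own tracing makes this matter: section 6.5.2.3.8 collects next-of-kin data when a traced woman has died, and 7.2.2.1 says the estimates include traced women. A tracing result can therefore change a woman's LTFU status while her retention status stays the same.

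At stake are whether the adjusted pooled estimate answers the primary question, and whether the stated power applies to it.

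**Working it through.** **1. Reproduce the plan's sample size.** Inputs from 6.4: p1 = 0.73 (SOC), p2 = 0.81 (CFL, 73% plus 8 points), n1 = 298, n2 = 894, two-sided 0.05. Two-proportion power with continuity correction:

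z = [ |p1 − p2| − 0.5(1/n1 + 1/n2) − 1.96·√(p̄(1 − p̄)(1/n1 + 1/n2)) ] / √(p1(1 − p1)/n1 + p2(1 − p2)/n2)

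- p̄ = (0.73 + 3 × 0.81)/4 = 0.79; 1/298 + 1/894 = 0.00447
- Numerator: 0.0800 − 0.0022 − 1.96 × 0.02725 = 0.0244
- Denominator: √(0.000661 + 0.000172) = 0.0289
- z = 0.84, power = 0.80

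Solving for n gives 298 SOC and 894 CFL, the plan's figures exactly. Without the correction, n is 282 SOC. The design figure therefore belongs to retention.

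**2. Compare the two outcomes on the 6.4.1 planning figures for SOC.**

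- Not retained: 1 − 0.73 = 0.27
- LTFU before tracing: 0.23. The other 4 points (4/27 = 15% of non-retention) are not LTFU events.
- Assumed deaths among LTFU women: 0.23 × 0.30 = 0.069
- LTFU if all those deaths are documented: 0.23 − 0.069 = 0.161
- Non-retention then outside the LTFU event: (4 + 6.9)/27 = 10.9/27 = 40%

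**3. Follow individual women through both definitions.**

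| Status | Retention (7.2.2.1) | LTFU (6.4.1, 7.1) |
|---|---|---|
| Lost, nothing further known | failure | event |
| Lost, traced, found to have died by 12 months | failure | not an event |
| Documented as stopped ART | failure | not an event |
| Documented transfer out | not stated | not an event |

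**4. Power with LTFU as the outcome.** The protocol gives no LTFU rate for CFL sites, so it has to be assumed. Same formula, same 298 and 894:

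| Assumption | SOC | CFL | Power |
|---|---|---|---|
| All 8 points come from LTFU | 23% | 15% | 0.85 |
| Reduction proportional (0.19 × 23/27) | 23% | 16.2% | 0.72 |
| First row, with the 30% who died removed from both arms (× 0.7) | 16.1% | 10.5% | 0.68 |
| Second row, with the 30% who died removed from both arms (× 0.7) | 16.1% | 11.3% | 0.53 |

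The 0.80 stated for retention therefore says nothing firm about LTFU.

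**The case against.** **Retention is modelled.** The sentence before the pooled model regresses retention on CFL model. Table 1 codes SOC as one level of that variable, and Objective 2 includes comparison with SOC, so a pooled contrast on retention could be derived from it. This stands. A reader might infer that the primary outcome has been dropped from the regressions, and the document does not support that. It does not remove the mismatch, because the pooled contrast and the component models are each specified in their own right with LTFU.

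**LTFU may be loose wording for not retained.** Table 3 puts all 27% of SOC mothers not in care under tracing, without separating the 23%. Against this, LTFU is defined twice with the exclusions, and section 6.5.2.2 abstracts in care, transferred, stopped, died and lost as separate statuses. No passage equates LTFU with non-retention.

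**The coding of deaths in the LTFU model is not stated.** This is true. Non-event status follows from the definition with all eligible women as denominator. Excluding or censoring these women would also depart from the retention definition.

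**Bias towards CFL.** It is tempting to argue that CFL providers trace defaulters, so deaths are better documented at CFL sites and LTFU looks lower there, by up to 6.9 points against an 8-point target. The documents do not support that as a finding. Section 2.0 says SOC staff also trace defaulters. Section 6.5.2.3.8 has the study trace lost women without distinguishing arms. Section 7.2.2.1 corrects all estimates from the sampled pairs. The 6.9 points would need one arm to document every death and the other none. A woman lost at 12 months who died later would also still be LTFU at 12 months.

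**Conclusion.** The concern holds as a mismatch of outcome. The protocol powers the any-CFL contrast on retention and states its component hypothesis on retention, but names LTFU as the maternal outcome in both sets of models. This is something the protocol states, not detail left for the analysis plan.

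The size on the planning figures is 27% not retained against 23% LTFU in SOC, with 16.1% as the floor if all assumed deaths among lost women are documented in time. The 4%, 23% and 30% are assumptions made for projecting sampling weights at the time of cohort construction, not 12-month results, so these shares are illustrative. The power range of 0.53 to 0.85 rests on assumed CFL rates.

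Differential documentation of deaths between CFL and SOC sites could bias an LTFU contrast, but neither its direction nor its size is established; 6.9 points is a hypothetical upper bound. Even with equal documentation, documented deaths would not count as events, so a difference in survival between the groups would not be properly reflected in the LTFU result.

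**What to change.** In 7.2.2.1, replace 12-month maternal LTFU in the any-CFL model and in the component models with 12-month retention (alive and in care, as already calculated in that section), or with its complement, not retained: dead, stopped ART or LTFU.

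State explicitly how documented transfers out are counted, and apply the same rule to the retention proportion. Pointing to the existing definition is not enough: the retention calculation gives no transfer rule, and the censoring at transfer date in 7.2.2.1 is written for survival outcomes.

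Keep LTFU as a secondary or descriptive outcome.

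The cost is a wording change plus one decision on transfers. The status categories needed are already abstracted under 6.5.2.2, so no new data are required, and the sample size in 6.4 then applies to the outcome for which it was calculated.

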CHWs are a trained cadre of lay health worker that promote public health, link clinics and communities through referrals and home visits, and enhance uptake and delivery of health services. CHWs may facilitate or directly provide a host of health services in response to the clinical and public health issues faced by their communities, ranging from counselling on maternal health and breast-feeding, supporting persons with mental illness, managing malaria and other uncomplicated paediatric diseases, and providing health education for chronic conditions such as HIV/AIDS, tuberculosis, and non-communicable diseases, among others. How CHWs are organized can vary widely based on their employer (i.e. government versus civil society), training and supervision, and compensation and opportunities for career progression. In SSA, CHWs have been deployed in numerous HIV care and ART programmes in a variety of country contexts. In Zambia, peer CHWs have been trained to provide home-based support and counselling for ART adherence, resulting in greater task shifting of health care worker responsibilities and decreased loss to follow-up in the national HIV programme. In Rwanda, a community-based HIV treatment programme providing comprehensive psychosocial support to PLHIV on ART, including longitudinal accompaniment offered by CHWs, resulted in 92% programme retention at 24 months post-ART initiation.

In Malawi, lay CHWs have been involved in a number of community-based care and treatment programs, including for palliative care, HIV-associated malignancies, and ART/ PMTCT, among others. For PMTCT, the *Tingathe* program provides a modest work-related stipend to CHWs who support HIV-infected pregnant women and their children from the time of their first ANC visit through

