breastfeeding cessation or successful ART initiation for infants diagnosed with HIV infection. Using this approach, the *Tingathe* program has catalysed improvements in ART uptake (and uptake of other ARV prophylactic regimens prior to Option B+ introduction), facility-based delivery, infant PMTCT prophylaxis, and EID testing. Similarly, Partners In Health—Malawi/ Abwenzi Pa Za Umoyo (APZU), established a CHW program in 2006 to support primary care service delivery in rural Neno District. The APZU program employs over 700 trained CHWs district-wide who serve as health educators, accompany patients with HIV, TB and other maladies to health facilities, and strengthen linkages for patients to the formal health system, including for PMTCT services.

Mentor mothers are mothers living with HIV who are employed, trained, and supervised to support health workers in under-resourced health facilities to deliver services as part of the health care team. The impact of mentor mothers has been reported previously from PMTCT programs throughout SSA. In Zimbabwe, a MSF-managed program demonstrated that clients receiving mentor mother support were twice as likely to return with their infants for EID testing compared to unsupported clients. Clients interviewed in this program reported decreased stigma, greater empowerment, and increased agency to disclose their HIV status to their male partner(s) and successfully negotiate condom use. In Uganda, the mentor mother model improved 12-month ART retention for HIV-positive mothers at mothers2mothers-supported facilities compared to clinics without mothers2mothers (m2m) services (90.9% vs. 63.6%, respectively). Assessment of MTCT at the end of breastfeeding demonstrated a durable impact to the m2m model, with the rate of HIV acquisition among 18-month-old infants being 6.8% in m2m-supported facilities compared to 8.7% in facilities without m2m. In South Africa, the presence of mentor mothers yielded favourable results on process indicators for HIV status disclosure, clinic attendance, and safe breastfeeding practices. In Malawi, m2m manages mentor mothers in over 100 clinics nationally who lead group and individual counselling sessions to provide psychosocial support and health education to new mothers and pregnant women living with HIV.

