## 6.3 Study Population

We will begin our study by reviewing existing data from a generalizable sample of women (and their infants/ young children) from selected facilities in the 5 districts meeting the following eligibility criteria:

- Newly diagnosed or having documented evidence of HIV infection between July 1, 2016 and June 30, 2017 in selected health facilities;
- Documented referral to or enrolment in Malawi's PMTCT/ ART program;
- Pregnant (at any gestational age) or breastfeeding at the time of HIV diagnosis/ positive HIV status identification;
- $\geq 16$  years of age at the time of PMTCT referral/ enrolment (includes adults and emancipated minors according to Malawi law);
- Received Antenatal or PMTCT services at a facility catchment area served by a CFL model of interest or SOC.

Existing, routine data for these women and their infants will form the basis for our full retrospective cohort. From these data, we will randomly select women and their infants (i.e. mother-infant pairs) to participate in the nested cohort.

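### The breastfeeding subgroup is defined by when ART was started, which the protocol also analyses as a possible effect of CFL, so the within-subgroup CFL contrast can be biased in either direction

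*Protocol*

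**What the plan says.** Protocol 7.2.2.1 sets out the model: "We will estimate the effect of receiving any CFL service on the risk of 12-month maternal LTFU and viral suppression". It then adds "we will conduct a sub-group analysis for women who initiated ART while breastfeeding". The covariates it names include neither pregnancy or breastfeeding status at HIV identification nor time from identification to ART, although the list is left open.

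The same section treats ART timing as an outcome of the models. Days from enrolment to ART start are calculated "to examine the effects of CFL models on time to ART initiation", and "We will look for differences in the delay of ART initiation across the CFL models and SOC". The secondary outcomes in 7.1 list "Median time from PMTCT enrolment to maternal ART initiation".

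Section 6.3 makes a different, earlier status part of eligibility: "Pregnant (at any gestational age) or breastfeeding at the time of HIV diagnosis" (or at identification of positive status).

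**The concern.** Take a woman whose HIV is identified in pregnancy. If she starts ART promptly she is outside the subgroup; if her start slips past delivery she is inside it. Where CFL affects how fast women start, the same woman could be in the subgroup at one type of site and out of it at another. Comparing CFL with SOC inside that subgroup means selecting on a consequence of exposure. Any difference in retention between late starters and women first identified while breastfeeding then shows up as an apparent CFL effect.

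The pathway is plausible on the protocol's own account. Section 3.0 describes a community health worker programme whose staff "support HIV-infected pregnant women and their children from the time of their first ANC visit through" the end of breastfeeding or infant ART start, so support can precede ART, and says that the "program has catalysed improvements in ART uptake". Section 2.0 puts the share of HIV-positive pregnant women who do not start ART at up to 15%, so initiation is not universal. That figure is about non-initiation, however, not delay.

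At stake is the interpretation of one subgroup result for 12-month loss to follow-up and viral suppression.

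**Working it through.** **Plan's own figures.** The protocol gives no number for this subgroup. The yardstick is the 8-point difference in 6.4. With 73% vs 81%, two-sided alpha 0.05, 80% power, 3:1 allocation and a continuity correction, the calculation returns 298 SOC and 894 CFL mothers, as stated. That figure is not in dispute.

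**Set-up.** Assume CFL has no effect on retention within either type of woman. Let

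- f = share identified while breastfeeding
- d = share of pregnancy-identified women whose ART start slips into breastfeeding
- r_bf, r_del = 12-month retention in women identified while breastfeeding and in late starters

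The share of late starters in the subgroup is w = (1−f)d / [f + (1−f)d], and subgroup retention is (1−w)·r_bf + w·r_del. The spurious difference, CFL minus SOC, is therefore

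(r_bf − r_del) × (w_SOC − w_CFL).

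It is zero when r_del = r_bf or when delay is equal in the two arms. Its sign depends on both factors.

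**Inputs.** r_bf = 73% borrows the protocol's overall SOC retention (6.4). Everything else is assumed: f 15–40%, d 10–30% in SOC and 5–10% in CFL, r_del 50–60%.

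**Middle of the range** (f = 25%, d = 20% vs 10%):

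- w_SOC = 0.15/0.40 = 0.375; w_CFL = 0.075/0.325 = 0.231
- r_del = 60%: retention 68.1% SOC vs 70.0% CFL, a difference of 1.9 points
- r_del = 50%: 64.4% vs 67.7%, a difference of 3.3 points

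**Ends of the range:**

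- Smallest: d = 10% in both arms gives 0.
- Largest: f = 15%, d = 30% vs 5%, r_del = 50%. w_SOC = 0.255/0.405 = 0.630 and w_CFL = 0.0425/0.1925 = 0.221. Retention is 58.5% vs 67.9%, a difference of 9.4 points.

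**A second set of assumptions** (f = 20%, d = 15% vs 5%, r_bf = 75%, r_del = 55%): 0.216/0.32 = 67.5% SOC vs 0.172/0.24 = 71.7% CFL, or 4.2 points. The risk ratio for not being retained is 28.3/32.5 = 0.87 with no true effect.

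**Reversal.** If late starters are retained better (r_bf = 65%, r_del = 75%), with f 10–30% and delay 10–20% in SOC vs 5% in CFL, the difference is −0.8 to −3.3 points. For example, f = 10% and d = 20% vs 5% gives 0.200/0.28 = 71.4% vs 0.09875/0.145 = 68.1%. The sign can also turn against CFL if CFL brings poorly retained women who would otherwise never have started ART into the subgroup.

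**With status at identification instead.** Late starters no longer enter the subgroup, so w = 0 in both arms and this mechanism contributes 0 in every scenario.

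**The case against.** Several points on the other side stand.

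- **Size is unsupported.** No section gives the share of women who delay ART past delivery. Section 6.5.2.3.7 says routine care starts ART as soon as possible, and 6.1 places the cohort after universal test-and-treat had stabilised. Both suggest a small share; the 30% at the top of the range has no support in the protocol.
- **Direction is not fixed.** A reader might infer that SOC must hold more late starters and that the bias must flatter CFL. The protocol only plans to look for differences in delay, its central hypothesis (4.0) does not mention time to ART, and the sign can reverse.
- **The alternative is not perfectly clean.** Section 3.0 credits lay-worker programmes with early promise for HIV testing uptake, and 7.1 lists testing as an outcome. CFL could therefore influence whether a woman is identified in pregnancy or while breastfeeding.
- **The endpoint itself runs from ART start** (6.5.2.1). Women who never start have no 12-month post-ART outcome under either definition.
- **Reach is narrow.** This is one subgroup in a paragraph that describes itself as exploring associations. A separate analysis plan could add covariates.

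The last point does not cure the problem. The protocol states the definition, and adjusting within a group selected on ART timing would not fully remove the selection. The remaining points limit the size and certainty of the bias; they do not change what the subgroup conditions on.

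**Conclusion.** The definition is flawed as written: it restricts on a variable that the protocol analyses as a possible effect of the exposure. Bias follows if CFL changes ART delay and late starters differ in retention. Under the assumed ranges it is 0 to 9.4 points in favour of CFL, with 1.9 to 3.3 points in the middle case; under other plausible inputs it is negative. Apart from the 73%, every input is an assumption, and prompt routine ART may make the real figure small.

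Two stronger readings should be resisted. The protocol does not show that the subgroup will produce a false CFL benefit, only that it could create, hide or reverse one. Nor does this touch the primary full-cohort comparison, which does not use the subgroup definition. The change is worth making because it is cheap and removes this mechanism, not because the main result is in doubt.

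**What to change.** In 7.2.2.1, define the subgroup as women who were breastfeeding, as opposed to pregnant, when HIV was diagnosed or positive status identified. Keep ART start during breastfeeding as a descriptive or sensitivity analysis, with a sentence noting that it selects on timing CFL may affect.

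The cost is a phrase in the analysis section. Section 6.3 already needs this status to establish eligibility, but the abstraction lists in 6.5.2.2 and 6.6.3 do not name it as a data item, so for some women it may have to be derived from test and delivery dates. Two limits should be stated alongside: the status could still be influenced by CFL effects on HIV testing, and it does not by itself give women who never start ART a 12-month post-ART outcome.
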